**Methods:**

In total, 284 senior citizens with CNLBP will be recruited in this single-centre, randomised, single-blinded (outcome assessors, data managers and the statistician), parallel controlled trial. Participants will be randomly divided into either one of three TC groups (1, 3, or 5 sessions/week, on the basis of weekly health educational lectures) or weekly health educational lectures, sustaining for 12 weeks, followed by 12 weeks of follow-up after the end of intervention. The primary outcome (the changes of LBP intensity at rest) will be measured at baseline before randomisation and immediately after the completion of weeks 4, 8 and 12 of the intervention, and the end of follow-up (week 24) using the visual analogue scale (VAS, 0–10 cm) to put a mark on the VAS scale to show how severities of their average low back pain have been over the past 24 h. Secondary outcomes, including Beck Depression Inventory-II, Pain Catastrophising Scale and Five Facet Mindfulness Questionnaire, Oswestry Disability Index and Short Form-36, will be measured at baseline and immediately after the completion of week 12 of the intervention and end of follow-up. The intention-to-treat and per-protocol principles will be used to analyse outcomes with a setting at *α* = 0.05 as statistical significance.

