#### Eligibility criteria

This trial will include the following: participants who are right-handed; adults aged 60 years or above [26, 27]; diagnosed with CNLBP for at least 3 months in line with the CNLBP definition of the National Institutes of Health (NIH) [30]; VAS score ≥ 4 [31]; Mini-Mental Status Examination (MMSE) score ≥ 24 [32]; no habitual regular exercise and TC training history in the past 6 months; able to ambulate independently and participate in TC training.

The exclusion criteria include the following: LBP caused by mandatory spondylitis, malignant tumours, vertebral fractures and spinal infection; serious diseases that limit ability to participate in TC training, including dementia, neurological disease, symptomatic heart or vascular disease (angina, peripheral vascular disease, congestive heart failure and severe hypertension), recent stroke, severe insulin-dependent diabetes mellitus, psychiatric disease, renal disease, liver disease, active cancer or anaemia; having analgesic drugs or regular physical therapy programmes for CNLBP within the past year; participating in a similar study within the past year and could have significant impact on the results of this study; planning to move permanently from the area during the trial period.

The withdrawal criteria comprise occurrence of severe adverse events (e.g. nausea, vomiting, palpitations) during the study and patients deemed unsuitable to continue the trial by specialist doctors; and voluntary withdrawal from the trial for any reason at any time.

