### Randomisation and blinding

The simple stochastic method will be applied in this study. SPSS 24.0 (IBM, Inc., Chicago, USA) software will be used by a statistician who is not involved in this study to generate a random number sequence. Random numbers with the group allocation code will be kept in opaque and sealed envelopes, which will be prepared by a person who is not involved in the whole process of the study, including recruitment, enrollment, evaluation and statistical analysis of data and random assignment the participants to the four groups (word “1” or “2” or “3” or “4”) with equal probability according to the order of entry. Random assignment results in all enrolled eligible participants will be informed by telephone after completing baseline assessment data collection and signing an informed consent form.

Considering the nature of TC, blinding the participants and TC coaches during the process of TC training is completely impossible. Hence, outcome assessors, data managers and the statistician will be blinded in this trial, and the blind will be kept by the custodian of the random sequence, who is not participating in the process of participant recruitment, intervention, outcome evaluation and data statistical analysis. Upon completion of all data analysis, the random sequence custodian will reveal the treatment allocations.

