#### Control group: health education

The control group will keep their daily lifestyle and will not receive any rehabilitation treatment during the intervention, except for one health lecture per week for 12 weeks.

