### Safety evaluation

Regardless of the reason for withdrawal during the process of intervention and follow-up period, we will figure out and detailed record the reasons for the withdrawal of participants in the case report forms (CRFs). If the participants experience any adverse events (AEs, defined as any impairment caused by TC training), the nurses will handle the AEs at once and contact the relevant research assistant. The details of AEs, including the time of occurrence, duration, degree of symptoms and treatment measures, will be recorded by the assistant in CRFs.

The doctor will provide comprehensive consideration to evaluate their correlation with clinical intervention training, who will advise whether the participant could continue to participate in the following study and give any medical treatment to relieve uncomfortable symptoms. Meanwhile, such events will be reported by the Ethics Committee. Then, the assistant in CRFs will calculate and record the incidence of adverse events via the following formula: Incidence of AEs (%) = (sessions with AEs / total exercise sessions in this group) × 100%, to measure the safety concerns. In addition, we will try to contact such participants and expect them to complete the follow-up.

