### Statistical analysis

The SPSS 24.0 software will be used to perform statistical analysis, and the primary outcome is the changes of LBP intensity at rest (week 12 minus baseline [week 0]). Firstly, we will compare the differences between each experimental group and the control group sequentially via using analysis of covariance (ANCOVA), adjusted for the baseline values of the VAS pain scores. The significance level of primary outcome will be set as *α* = 0.0167. If significant differences are observed amongst the three experimental groups, we will use the fixed-sequence test to compare the differences between TC group (1 session/ week) and group (5 sessions/ week); group (1 session/ week) and group (3 sessions/ week); group (3 sessions/ week) and group (5 sessions/ week) sequentially using analysis of covariance, and the significance level of fixed order test will be set as *α* = 0.05. Treatment effects with corresponding 95% confidence intervals will be presented. The intention-to-treat (ITT) will be used to analyse the primary and secondary outcomes when participants have completed randomisation and received treatment for at least 4 weeks. Then, the per-protocol (PP) analysis of the primary outcome will be used as a sensitivity analysis when participants have completed 12-week intervention and have a compliance rate of > 85%. The results of ITT and PP analysis will be compared to check the consistency of results. The missing data will be adjusted by the multiple imputation method. In addition, multivariate regression analyses will be performed to examine the effect of the TC training on the primary outcome measure, adjusting for variables in the baseline data, such as age, sex, and the level of physical activity, to verify the consistency of the results between analysis of covariance and multivariate regression analysis, and further to improve the reliability of the results. Mediation analysis will be performed through a series of linear regression models to evaluate the strength of the relationships amongst the treatment/control group, the mediator and pain outcome to identify whether baseline mindfulness of participants mediates the effect of TC on treatment outcomes.

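### The analysis set labelled ITT admits only participants treated for at least 4 weeks, so it is selected after randomisation and leaves the comparisons open to bias.

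*Protocol article*

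**What the plan says.** Four statements in the protocol article bear on who is analysed.

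- **Abstract, Methods.** "The intention-to-treat and per-protocol principles will be used to analyse outcomes". No condition on treatment received is attached.
- **Statistical analysis, ITT.** ITT is used to "analyse the primary and secondary outcomes when participants have completed randomisation and received treatment for at least 4 weeks".
- **Statistical analysis, per-protocol.** The sensitivity analysis of the primary outcome takes those who have "completed 12-week intervention and have a compliance rate of > 85" per cent.
- **Statistical analysis, missing data.** "The missing data will be adjusted by the multiple imputation method". Nothing says that this brings back people who fall outside the set.

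Three other sections show how people can leave and what is then done. Eligibility criteria allow "voluntary withdrawal from the trial for any reason at any time", so leaving can fall before week 4. Safety evaluation says of those who withdraw that "we will try to contact such participants and expect them to complete the follow-up". Control group: health education says that controls receive no rehabilitation "except for one health lecture per week for 12 weeks".

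**The concern.** Randomisation makes the arms comparable as they were allocated. Once membership of the analysis set depends on something that happens later, that guarantee is lost, whatever the set is called.

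Early leaving could plausibly depend on the arm here. The Tai Chi arms are asked for one, three or five supervised hours a week on top of the lecture, and controls for the lecture alone. The section Randomisation and blinding says that "blinding the participants and TC coaches during the process of TC training is completely impossible", and participants learn their allocation by telephone. The Discussion itself links adherence and pain coping to the benefit obtained from exercise, so staying and responding may go together.

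Two questions are at stake: whether Tai Chi beats the lecture, and which weekly frequency is best. For the second, being unable or unwilling to keep up a frequency is part of the answer that a clinician needs. A set that removes those who stop early answers a narrower question than the one the trial poses.

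**Working it through.** **1. Is the 4-week condition a rule of membership?** The ITT and per-protocol sentences are built alike: each names a principle and then the condition that participants must meet. The second plainly defines a set, so the first does too. The condition concerns treatment received, not a measurement obtained.

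**2. Does anything restore the excluded?** The per-protocol set is stricter (12 weeks and more than 85% compliance). Imputation is stated without any extension of the set. Safety evaluation seeks follow-up from people who withdraw, and the 4-week rule would then discard whatever is obtained from the early ones. All participants have a VAS from before randomisation, so missing baselines do not force the exclusion.

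**3. The plan's attrition figure.** Inputs from Sample size: 60 per group before attrition (240/4) and 15% attrition. 60/(1 − 0.15) = 70.6, rounded up to 71; 4 × 71 = 284. This reproduces. The 15% is total attrition; the article gives no share before week 4 and none by arm. I therefore assume 5–15% of a Tai Chi arm, where 15% puts all planned attrition before week 4. That is 0.05 × 71 = 3.6 to 0.15 × 71 = 10.7, or about 4 to 11 people per arm.

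**4. Illustration for Tai Chi versus control.** Assume that stayers gain 2.0 cm over control (the difference used in Sample size), leavers gain nothing and no controls are excluded. Effect in all randomised = 2.0 × (1 − e).
- e = 0.05: 1.9 cm; 2.0/1.9 = 1.05.
- e = 0.15: 1.7 cm; 2.0/1.7 = 1.18.

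**5. General form.** Let q be the share excluded from an arm and g the amount (cm) by which the excluded fare worse than stayers in that arm. Bias in the comparison = q(TC) × g(TC) − q(control) × g(control). With none excluded from control:

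| q | g = 1 cm | g = 2 cm |
|---|---|---|
| 5% | 0.05 | 0.10 |
| 10% | 0.10 | 0.20 |
| 15% | 0.15 | 0.30 |

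If the two products are equal, or if g = 0, the bias is zero. If 15% of controls left early with g = 2 and nobody left a Tai Chi arm, it would be −0.30 cm, against Tai Chi.

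**6. Type I error in the one-sided-exclusion case.** Assume no true effect in all randomised, SD 2.2, 71 randomised per arm and a two-sided test at 0.0167 (critical value c = 2.39). With b = q × g and se = 2.2 × √(1/71 + 1/(71(1 − q))), the error is Φ(b/se − c) + Φ(−b/se − c). For q = 0.15 and g = 2, se = 0.385, b/se = 0.78 and the error is 0.054. Over q = 5–15% it runs from 0.018 to 0.025 for g = 1 and from 0.021 to 0.054 for g = 2.

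**7. Illustration for frequencies.** If 5% of the once-weekly arm and 15% of the five-times-weekly arm left early, and stayers in both gained 2.0 cm, all randomised would show 1.9 − 1.7 = 0.2 cm in favour of once weekly. The 4-week set would show 0. For scale, the standard error of a two-arm difference is about 2.2 × √(2/71) = 0.37 cm.

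**8. Would imputation alone repair it?** I simulated step 4 at its upper end: 71 per arm, 11 Tai Chi leavers without benefit, baseline-adjusted ANCOVA, 2,000 trials, 20 imputations. Mean estimates:
- all randomised with week-12 data observed: 1.69 cm (by hand, 2.0 × 60/71 = 1.69);
- leavers excluded: 2.00 cm;
- leavers imputed from arm and baseline, missing at random: 2.00 cm.

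Such imputation treats a leaver with only a baseline value like a stayer in the same arm, and removes none of the difference.

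**The case against.** The strongest reply is that the harm is not shown. Bias needs exclusion that is related to outcome and unequal across arms, and the article gives no early-dropout rate. The upper figures in the illustration stack assumptions: all attrition before week 4, none of it in controls, no benefit in any leaver. The 0.2 cm frequency example is a tenth of the 2-point difference used for the sample size and about half a standard error. All of this stands, and it limits the point to exposure to bias.

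Three stronger readings are tempting, and the documents do not support them.

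- A reader might infer that the effects *are* biased. That cannot be known from the plan.
- A reader might infer that the rule favours the most demanding arm. Unblinded controls offered only a lecture may also leave early, and if those who leave fare worse, excluding them would shrink the Tai Chi effect. Nothing in the article settles which dominates.
- A reader might infer that no planned analysis covers everyone randomised. The multivariate regression of the primary outcome has no stated set. It may inherit the 4-week set, but the text does not say so.

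It can also be said that week 4 is the first VAS after baseline, so this resembles a modified ITT set under the wrong name. The article does not give that reason, and the rule is worded on treatment rather than measurement, so the mitigation is slight. Finally, redefining the set and imputing would not by itself change the estimate, as step 8 shows. That is right, and it shapes the remedy.

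**Conclusion.** The point holds as a defect of definition. The label does not match the rule, the rule conflicts with the principle in the abstract, and the other stated set is narrower. It is a stated rule, not a detail left to an analysis plan. It governs every primary and secondary comparison and would set aside outcome data that the trial intends to seek.

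The consequence is exposure to bias of unknown size and sign. Under the one-sided assumptions used above it is 0.1–0.3 cm on a 2.0 cm effect (the all-randomised effect overstated by 5–18%). It is near zero if early exclusion is unrelated to outcome or alike in all arms. These figures are illustrations, not estimates for this trial.

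**What to change.** Before allocation is revealed, change the Statistical analysis section as follows.

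1. Define ITT as all randomised participants, analysed in the arm assigned, regardless of sessions received.
2. State that the week-12 VAS of participants who stop training is included, using the follow-up already planned under Safety evaluation. Most of the gain comes from this step.
3. Use multiple imputation only for values still missing, and add a sensitivity analysis that assumes a less favourable outcome for early leavers than for stayers in their arm.
4. If the 4-week set is wanted, keep it under its own name (modified ITT) as a sensitivity set.

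The cost is a little more analysis work and possibly a smaller estimated effect. The planned 284 participants and the visit schedule do not change. The benefit depends on how many early leavers are actually measured at week 12.

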## Abstract

**Background:**

Tai Chi (TC), as one of mild to moderate exercise therapies specifically recommended by clinical practice guideline from the American College of Physician, is a viable option for chronic non-specific low back pain (CNLBP) treatment. Nevertheless, limited studies focused on the effect of different weekly frequencies of TC in elders with CNLBP. This superiority study aims to compare the differences of TC with different weekly frequencies in elders with CNLBP on the premise of proving its effectiveness, and identifying whether mindfulness mediates the effect of TC on treatment outcomes.

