In light of the abovementioned studies, the primary objective of this study will compare the differences in the curative effects of TC with different weekly frequencies in elders over 60 years [26, 27] with CNLBP on the premise of proving its effectiveness. Besides, we will also identify whether mindfulness mediates the intervention effect of TC. We hypothesised that high weekly frequencies (five times a week) of TC intervention may be more beneficial to pain, physical and psychosocial functioning and QOL in elderly with CNLBP than low (once a week) and moderate weekly frequencies (three times a week) TC intervention, and that the higher the baseline mindfulness level of participants, the better the effect of TC on CNLBP symptoms. The interventions are relatively safe. The results of this trial are expected to help clinicians and future researchers provide references in selecting the ideal TC dose and standardise the formulation of TC exercise prescription for patients with CNLBP, and enrich the theoretical basis for TC dose selection. For patients, we expect the results of this study to provide evidence-based advice for treatment planning for patients with CNLBP and to use TC as an ideal form of self-care to relieve their symptoms and improve QOL.

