## Methods and analysis

### Trial design

This study is a single-centre, randomised, single-blinded (outcome assessors, data managers and the statistician), parallel controlled trial, which will be carried out in Changsha First Social Welfare Institute, Hunan Province, China. In total, 284 eligible participants with CNLBP will be randomly and equally divided into four groups in a 1:1:1:1 allocation ratio. Three experimental groups will undergo 12 weeks of supervised TC training and complete one, three or five TC sessions weekly, respectively. The control group will not receive any rehabilitation programme. Meanwhile, all participants will receive weekly health lectures until the end of the 12-week intervention and will be required to maintain a healthy lifestyle, afterwards followed by 12 weeks of follow-up after the end of the intervention.

The primary outcome (the changes of LBP intensity at rest) will be measured at baseline before randomisation and immediately after the completion of week 4, week 8, week 12 of the intervention and the end of follow-up (week 24). The secondary outcomes will be measured at baseline before randomisation and immediately after the completion of week 12 of the intervention and the end of follow-up (week 24). The details of the time schedule of this trial are shown in Table 1. The recommendations of the Consolidated Standards of Reporting Trials (CONSORT) will be strictly followed, and the protocol will be reported in line with the Standard Protocol Items (SPIRIT) [28] (Additional file 2). The flow chart is presented in Fig. 1.

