Notably, mindfulness, as a complex psychosocial variable and a predictor for better health outcomes from exercise, should be paid more attention. Poor adherence and low pain-coping skills are regarded as the major hindrances to the effect of exercise in CNLBP, and mindfulness has been highly associated with pain-coping skills [61, 62] and superior adherence [63, 64]. A recent study indicated that regardless of the effectiveness of exercise, adherence in patients with CLNBP always declines considerably over time [65], which is probably closely related to improving the effectiveness of TC interventions in chronic pain. In addition, Hall et al.’s study [66] provided initial evidence that pain catastrophising, as one of the cognitive appraisal outcomes, has partial mediation, that is, it reduces about 1/3 of pain intensity and 2/3 of disability. Notably, a strong link between baseline mindfulness and the level of pain catastrophising has been verified in a previous study [61]. Lee et al.’s study also confirmed this relationship in patients with knee osteoarthritis, which seems to suggest that higher mindfulness corresponds to a better response to TC training [67]. Up to now, limited study has investigated the longitudinal regression and correlation of mindfulness on the therapeutic effect of TC. Hence, our study makes reasonable speculation that baseline mindfulness may also influence the effect of TC in elderly with CNLBP. The results will contribute to further understanding the heterogeneity of TC response in patients with chronic pain and help physicians to develop personalised exercise prescriptions for such patients.

However, this trial still has several potential limitations and challenges. Firstly, although we will conduct blinding as much as we can, no blinding is possible for coaches and participants in terms of treatment allocation, which is also an inherent limitation of such studies [17, 68, 69]. Secondly, although we will hire experienced coaches and establish a strict quality control programme for participants (e.g. monitor practice and sign-in), the degree of treatment efficiency may become uneven depending on the teaching level of each coach and the acceptability of participants. In short, we will standardise and normalise every step of the study as much as possible to ensure that high-quality evidence is obtained.

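### Baseline mindfulness is named as the mediator, but treatment cannot change it; the planned analysis tests neither the mediation aim nor the hypothesis, which is moderation

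*Protocol article*

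**What the plan says.** The protocol article describes the role of mindfulness in two different ways.

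- **Aim.** The Abstract (Background) gives a second purpose of "identifying whether mindfulness mediates the effect of TC on treatment outcomes", and the Introduction repeats it: "we will also identify whether mindfulness mediates the intervention effect of TC". Neither sentence says when mindfulness is measured.
- **Hypothesis.** The Introduction expects that "the higher the baseline mindfulness level of participants, the better the effect of TC on CNLBP symptoms". The Discussion gives the same rationale, citing work in knee osteoarthritis which suggests that "higher mindfulness corresponds to a better response to TC training".
- **Analysis.** The Statistical analysis section states: "Mediation analysis will be performed through a series of linear regression models to evaluate the strength of the relationships amongst the treatment/control group, the mediator". Pain is the third variable in these regressions. The purpose is "to identify whether baseline mindfulness of participants mediates the effect of TC on treatment outcomes".
- **Timing.** FFMQ is a secondary outcome (Abstract, Methods: "Secondary outcomes, including Beck Depression Inventory-II, Pain Catastrophising Scale and Five Facet Mindfulness Questionnaire"). Under Trial design, "The secondary outcomes will be measured at baseline before randomisation and immediately after the completion of week 12 of the intervention" and again at week 24. The Randomisation and blinding section adds that participants learn their allocation only after baseline data have been collected.

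**The concern.** A mediator has to lie between treatment and outcome: treatment changes it, and the change carries some of the effect to the outcome. A value recorded before randomisation cannot do this. The analysis as written therefore estimates a quantity that is zero by design.

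The hypothesis asks something else, namely whether the benefit of TC is larger in people who start with higher mindfulness. That is moderation, and it is tested by an interaction between arm and baseline mindfulness. Regressions that link group, mediator and pain in the usual mediation sequence do not contain that term, and the article mentions none.

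Two misreadings could follow. A null result, which is almost guaranteed, could be reported as evidence that mindfulness plays no part in the response to TC. A chance imbalance in baseline FFMQ could be reported as a mechanism. The Discussion intends to use the result to understand varying response and to personalise exercise prescription, and neither reading would support that.

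**Working it through.** The plan gives no effect size, power or sample size for this analysis, so there is no figure to reproduce. The check is algebraic, with a simulation as illustration.

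**Step 1: the indirect effect.** In the regression approach to mediation:

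- path a = difference between groups in the mediator;
- path b = slope of pain on the mediator, adjusted for group;
- indirect effect = a × b.

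With baseline FFMQ as the mediator, a = E(baseline FFMQ | TC) − E(baseline FFMQ | control). Allocation is random (1:1:1:1, Trial design) and comes after the measurement, so a = 0. The indirect effect is then 0 × b = 0 for every value of b.

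**Step 2: the chance of declaring mediation.** Joint significance requires both paths to be significant, so P(declare) ≤ P(path a significant) = 5% for one contrast tested at two-sided 5%. If each of the three TC arms were instead tested separately against the shared control, the chance of at least one significant path a would be about 12 to 13% (simulated, equal arms). That is still only the chance of a baseline imbalance.

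**Step 3: illustration.** The simulation used 4,000 runs of one TC group against control.

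| Input | Value | Source |
|---|---|---|
| Evaluable per arm | 240 / 4 = 60 | Sample size section |
| Residual SD of VAS | 2.2 | Sample size section |
| Mean TC effect | −2 VAS points | Sample size section (minimum clinically important difference) |
| Change in TC effect per SD of baseline mindfulness | −1 VAS point (greater benefit with higher mindfulness) | Assumption, not in the documents |

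Baseline mindfulness therefore truly modifies the effect in these data. Results:

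| Quantity | Result |
|---|---|
| Mean estimated indirect effect | −0.002 |
| Path a significant | 4.4% of runs |
| Sobel test of a × b significant | 0.5% of runs |
| Group-by-baseline-mindfulness interaction significant | 68% of runs |

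The planned approach misses the effect modification that is present, while an interaction test on the same data often finds it. The 68% depends on the assumed size of the modification. The zero indirect effect does not.

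**Step 4: aim, hypothesis and analysis compared.**

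| | Variable | Question | Answered by the planned analysis? |
|---|---|---|---|
| Aim | mindfulness, time not given | mediation | No: needs a value measured after randomisation |
| Hypothesis | baseline mindfulness | moderation | No: needs an interaction term |
| Analysis | baseline mindfulness | mediation | Indirect effect is zero by design |

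**The case against.** The best case for leaving the plan alone has four parts.

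- **The analysis is secondary.** The primary objective is the comparison of weekly frequencies. The primary ANCOVA, its significance level and the sample size do not depend on mindfulness. This is true and limits the reach of the problem. It does not rescue the mindfulness aim, which the Abstract and Introduction place beside the main objective.
- **The article gives no model terms.** A full protocol exists and is not shown, so an interaction might be specified there. It is fair to say only that the article mentions no interaction. But the fault lies in what the article does state: it puts a pre-randomisation variable in the mediator's role. A fuller document that followed this sentence would carry the same error, and one that used an interaction would be testing moderation under the wrong name.
- **The 5% bound assumes one contrast.** This is correct, and the figure rises to about 12 to 13% over three unpooled contrasts. The article's wording reads most naturally as a single treatment-versus-control variable, and under either reading the extra positives are chance imbalance.
- **The mediation aim is legitimate in itself.** The Abstract and Introduction do not say baseline when they state it, and FFMQ is measured again after treatment. This stands. The aim need not be abandoned, but it needs a different mediator from the one named. Nor is the word baseline likely to be a slip, because it recurs in the hypothesis, the analysis and the Discussion.

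**Conclusion.** The point holds. As written, the mediation analysis has a true indirect effect of zero and can answer neither the mediation aim nor the moderation hypothesis. The probability of a positive finding is at most 5% for one contrast, or about 12 to 13% for at least one significant path a across three separate contrasts, and every such finding would be spurious. The conclusion rests only on random allocation and on baseline FFMQ being measured before it, both of which the protocol states. The primary comparison is not affected. The correction should be made before the data are unblinded, because a model chosen afterwards would look data-driven.

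**What to change.** 1. **Test the hypothesis as moderation.** Add baseline FFMQ and the arm-by-baseline-FFMQ interaction to the week-12 VAS ANCOVA, keeping baseline VAS as a covariate. With four arms, state in advance whether this is a joint test over the three TC-versus-control interaction contrasts or a single contrast of pooled TC against control. Report the interaction estimates with confidence intervals.
2. **If mediation is also wanted, use a mediator measured after randomisation.** FFMQ is first repeated at week 12, the same visit as the primary outcome, so the mediator precedes the outcome only for week-24 pain. Take FFMQ change to week 12 as mediator and week-24 VAS as outcome, adjusted for baseline FFMQ and baseline VAS. Label the analysis exploratory, and state that its outcome differs from the primary week-12 change.
3. **Align the wording.** Wherever baseline mindfulness is meant, replace mediation with moderation. Keep the word mediation in the Abstract and Introduction only if item 2 is adopted. Make the Statistical analysis and Discussion sections match.

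The cost is the wording of the aim and one or two models. FFMQ is already scheduled at baseline, week 12 and week 24, so no visit, measurement or participant is added.
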